##### Exploratory analysis

We will analyze the observed skills for the experimental condition over the two practice SP interactions and examine if there is decay, maintenance or further growth in the test case scenario. Growth curve analyses will be used to test for linear change in observed suicide prevention skills across the three data collection points (two observations during a 4-month period and at the 6-month “test case” observation of all study participants at follow up). The HLM 7.0 statistical software package will be used for conducting growth curve and multilevel analyses [41]. Although attempts will be made to equate the time distance between observations for SP trainees, we do expect variability in the number of days between observations to exist across persons. Thus, time will be modeled to reflect change from baseline status (i.e., time 1 = 0; intercept corresponds to baseline status) and time will be a count of days from baseline to subsequent observations. Particular interest lies in the overall slope estimates (i.e., do skills change over time?) and predictors of change (slope). For example, the following questions will be addressed: “Does prior experience with suicidal individuals predict changes in skills over time?” Additionally, effect sizes (ES), based on the work of Feingold [42] will be examined. Estimates of the means at each time point are derived from the model and used for effect size calculations (mean difference divided by pooled standard deviation).

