### Procedures

Following enrollment, participants receive an email with instruction to complete online baseline assessments and view the teaching videos within 14 days. All surveys are completed online using the same secure website that hosts the CTL-PC videos. After they have viewed the videos, participants in the experimental condition engage in two practice SP interactions over a period of about four months, with at least one month between interactions. Participants in the control condition do not have practice interactions. At approximately six months following completion of online teaching, both experimental and control participants complete the same face-to-face SP test case. There are two SP character scenarios for the experimental practice sessions and one test case SP scenario.

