As part of their practice experience, experimental participants engage in telehealth and face-to-face SP interactions; the order of presentation is randomized. The SP practice character scenario is also randomized (male/female) for the experimental group. All interactions are video-taped for observational coding of suicide prevention skills. In the telehealth modality, the participant and standardized patient are in different locations and interact using a secure webcam service. The face-to-face modality occurs in an office setting. The procedures for face-to-face and telehealth interactions are the same and no more than one hour in duration, including: orientation to the procedures and the SP scenario backstory, up to 30 min for the SP interaction, 8 min for SP feedback for the participant, and 5 to 10 min for debrief procedures. Upon arrival to the interaction, participants are introduced to the procedures and are given a brief written backstory about the SP scenario. Backstories provide context for the provider and include details about the patient’s name, age, the nature of the patient-provider relationship, some medical and social history and the reason for this visit (“trouble sleeping”). Telehealth participants also receive instructions about remote access. Participants are instructed to assess the patient’s risk for suicidality and provide appropriate interventions within a 30-min timeframe (a timer signals the appointment end). After the interaction, participants exit the room for 10 min during which time the SP prepares immediate feedback (positive and constructive) for the patient. SPs are highly trained to prepare and deliver tailored feedback using a 15-item “feedback matrix” template of criteria for identifying appropriate feedback items. Feedback includes specific competency items with explanations and rationale for the importance of the skill. The participant joins the SP for 8 min to receive feedback, discuss the interaction and ask questions. Afterwards, the participant returns to the facilitator for 5 to 10 min of debrief procedures. During this time, participants are provided the opportunity to speak with a psychologist for further debriefing if needed.

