##### Standardized patient scenarios

Three scenarios were developed for the study with input from subject matter experts. Each scenario features an older adolescent/young adult primary care patient experiencing suicidal thoughts in the context of stressful life events. The three scenarios were matched for upstream factors (e.g., life stressors, social support) and difficulty. A male and a female scenario are modified slightly for telehealth interactions (experimental condition). The scenario used for the SP test case that all participants receive is an in-person female scenario. Choice of female gender for the test case reflects the greater proportion of suicide attempts in females.

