The primary hypothesis of the study is that participants in the experimental condition will demonstrate significantly better skills compared to the control group, as measured by reliable, observed ratings of behaviors in the SP assessment at 6 months. We will use ANCOVA to assess SP training effects at follow up on all participants’ skills. Skills will be measured by reliable observational ratings of several suicide specific and general interviewing skills. In all instances, gender, training program group, race/ethnicity, and age will be included as covariates to aid in statistical power [35, 36].

##### Exploratory analysis for hypothesis 3

We will examine statistical equivalence between the two SP modalities (face-to-face; telehealth). Similar to Hypothesis 1 (above), Tryon’s inferential confidence intervals will be used to assess for equivalency among face-to-face and telehealth modalities [31, 32]. Following Treadwell and colleagues [33], a standardized small effect of .20 [34] will define the criterion for establishing a MID. As a form of sensitivity, a MID of .10 will also be examined. As a second form of sensitivity, multilevel modeling will be used to decompose the variance associated with these observed training outcomes into variance attributed to the person as well as variance attributed to time (first SP interaction, second SP interaction) and variance attributed to modality. Since the order is randomized, we might expect more variance attributed to time (improving over time). Within these models, the learner (person) defines level 2 with the observed ratings being the dependent level one variables. Both time and modality will be entered as time varying covariates.

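### The three-session growth analysis cannot separate a change in skill from the switch to a new patient case at session 3

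*Protocol article*

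**What the plan says.** All references are to the Protocol article.

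- **Scenarios by session.** Procedures: "There are two SP character scenarios for the experimental practice sessions and one test case SP scenario". Standardized patient scenarios: "The scenario used for the SP test case that all participants receive is an in-person female scenario".
- **Randomised features of practice.** Procedures: "The SP practice character scenario is also randomized (male/female) for the experimental group", and "experimental participants engage in telehealth and face-to-face SP interactions; the order of presentation is randomized".
- **Matching.** Standardized patient scenarios states that the three cases were matched on background factors and on difficulty, with expert input. It gives no data on how they compare.
- **Growth analysis.** The Exploratory analysis that follows Hypothesis 3 says "Growth curve analyses will be used to test for linear change in observed suicide prevention skills across the three data collection points". It defines time by days: "time will be a count of days from baseline to subsequent observations". The aim is to "examine if there is decay, maintenance or further growth in the test case scenario". The predictors of slope it mentions are participant characteristics such as prior experience.
- **Modality model.** Exploratory analysis for hypothesis 3 uses the first and second interactions only: "Both time and modality will be entered as time varying covariates".

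**The concern.** A skill rating at one session is a rating on one particular patient case. In the experimental arm, the case at session 3 is always one that was not used before. The fitted line over days treats the three ratings as readings from the same instrument. If the third case is somewhat easier than the practice cases, the trend shows growth that did not occur. If it is harder, the trend shows decay. The error can also hide a real change: a true decay of .20 SD on a case that is .20 SD easier appears as maintenance (-.20 + .20 = 0).

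Modality adds a second, smaller confounder. Session 3 is always face-to-face, while each participant has one practice session by telehealth. The growth model as described names neither case nor modality.

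At stake is the exploratory answer on whether skills last until follow-up. Power analyses presents this as one of the useful products of the trial for dissemination.

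**Working it through.** The article gives no power or bias figure for the growth analysis, so there is no stated figure to reproduce.

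**Inputs from the document.** 108 participants (Participants) at 1:1 (Design) give 108/2 = 54 in the experimental arm. Alpha is .05 (Data processing), taken as two-sided.

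**Assumptions.** Session spacing, within-person correlation rho and residual case difference D (in SD units) are not given and are shown as ranges. True change is set to zero.

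**1. Can the data separate case from time?** With three free session means plus a test-case indicator, the design has 4 columns and rank 3, so the indicator is aliased with session 3. With linear days plus the indicator, the rank is 3 for 3 columns. The slope then rests on sessions 1 and 2 alone, and the indicator absorbs all departure from linearity. In neither model is test-case difficulty separated from decay or growth.

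**2. How much of D enters the fitted trend?** The least-squares weight of session 3 is (t3 - tbar) / sum of (t - tbar)^2. Multiplying by (t3 - t1) gives the share of D in the fitted first-to-last change. For months 0, 2, 5: tbar = 2.333, sum of squares = 12.667, weight = 2.667/12.667 = .2105, share = .2105 x 5 = 1.05.

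| Months of sessions | Share of D |
|---|---|
| 0, 1, 5 | 1.07 |
| 0, 2, 5 | 1.05 |
| 0, 2, 4 | 1.00 |
| 0, 3, 5 | 0.92 |
| 0, 4, 6 | 0.86 |
| 0, 4, 5 | 0.71 |

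**3. False change from session 2 to the test case.** For a paired t-test, SE = sqrt(2(1 - rho)/54). This is sqrt(1/54) = .136 at rho .5 and sqrt(.6/54) = .105 at rho .7. The rejection probability comes from the noncentral t distribution with noncentrality D/SE.

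| D | rho .5 | rho .7 |
|---|---|---|
| .10 | .11 | .15 |
| .20 | .30 | .46 |
| .30 | .58 | .80 |

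**4. The same question for the linear slope that the plan names.** This was a simulation with 54 participants and sessions near months 0, 2 and 5 with some variation. At within-person correlation .5, the slope was significant in 5% of runs for D = 0, 11% for .10, 33% for .20 and 62% for .30. At D = .20 the range was 24% to 50% for correlations of .3 to .7.

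**5. Modality comparison.** Only sessions 1 and 2 enter, and both practice case and modality order are randomised. In simulation, a male/female case difference of .1 to .5 SD gave a bias of at most .002 SD (simulation error) and rejection of about 5%. The cost is precision: the SE is multiplied by sqrt((2(1 - rho) + D^2) / (2(1 - rho))). At rho .5 and D = .10 this is sqrt(1.01), or 0.5%. At rho .7 and D = .30 it is sqrt(.69/.60), or 7%. The formula assumes that each participant meets both practice cases once, which the article does not say outright.

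**The case against.** **The cases were matched.** The article states matching on difficulty, and no figure in it supports a residual difference of .20 or .30 SD. This stands in part. A reader might infer that case difficulty is in fact being read as learning or decay; the document does not show that. Matching by experts without calibration data reduces the risk but does not rule out a difference as small as .20 SD, the article's own minimum important difference for the modality comparison.

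**The article is condensed.** A full list of model terms is commonly left to the full protocol or analysis plan, and the slope predictors here are introduced only as examples. This stands as far as a missing term goes. A reader might take the absent scenario term to be the fault. It is not, because no such term can separate the third case from session 3. The fault lies in the three-point trend and the reading attached to it, both of which the article states.

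**The modality model is sound.** This stands. A reader might extend the problem to that comparison because it also names no scenario term. The test case never enters it, and the practice factors are randomised, so only a little precision is lost. For the same reason the session 1 to 2 change is not biased on average.

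**The analysis is exploratory and the primary result is safe.** Both points stand. Both arms receive the same test case, so its difficulty cancels in the between-arm comparison. This limits the weight of the point but does not make the decay-or-growth reading interpretable.

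**Conclusion.** The point holds for the exploratory growth analysis only. As written, the trend over three sessions and the reading at the test case mix change in skill with any residual difficulty of the third case, and with the move to all face-to-face. More participants would not help.

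Under 54 participants, no true change and a within-person correlation of .5 to .7, a residual difference of .20 SD gives a false session 2 to test-case change about 30% to 46% of the time. At .30 SD this is 58% to 80%. About 0.7 to 1.07 of the offset passes into the modelled first-to-last change. These sizes rest on assumed case differences, correlations and session times. If the matching was exact and modality has no effect, the error rate stays at its nominal 5%.

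**What to change.** 1. Base the learning claim on sessions 1 and 2, with practice case (male/female) and modality as covariates.
2. Add practice case to the multilevel model under Exploratory analysis for hypothesis 3, beside time and modality, to recover the small loss of precision.
3. Report the session 2 to test-case change separately, and state that it is confounded with the new case. Give a sensitivity range for case difficulty, for example plus or minus .10 to .30 SD. Do not call the change decay or growth unless the conclusion holds over that range.
4. Do not rely on a test-case term in the three-point model.

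The cost is revised analysis wording and one covariate that the trial already randomises; no new data are needed. The price is a weaker exploratory claim. With 54 participants the 95% half-width is 2.006 x .136 = .27 SD at rho .5 and 2.006 x .105 = .21 SD at rho .7. An observed change would have to exceed about .57 or .51 SD to hold over the full .30 SD range, and about .37 or .31 SD to hold over .10 SD.

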### Design

The study is a randomized controlled trial with an experimental group and a control group allocated with a 1:1 randomization ratio. All trainees are randomized to control and experimental learning groups using Wei’s urn randomization [23] which provides overall balance at the end of accrual but also gives good, often near-perfect, balance within many strata [24, 25]. Randomization strata include medical learner groups (i.e., medical residents, pediatric residents, and nurse practitioners) and gender. After all baseline measures are completed, participants are randomized to experimental condition by the project statistician, who remains blinded to study condition.

Participants in both groups complete a 48-min, 6-module, online video-based training on suicide prevention (Commitment to Living for Primary Care; CTL-PC). Upon completion of the online teaching program, participants in the experimental group engage in two standardized patient practice interactions over the course of 4 to 6 months. One practice interaction takes place in-person and the other uses a telehealth model. The order is randomized. Then, approximately 6 to 8 months (depending on schedules, see below) after video-based learning, both control and experimental groups engage in an in-person “test case” standardized patient interaction.

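### A single linear slope over three sessions, with no modality term, cannot separate decay from growth at the test case and would read a telehealth handicap as learning

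*Protocol article*

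**What the plan says.** The stand-alone Exploratory analysis, at the end of Hypotheses and exploratory analyses, concerns the experimental arm's two practice sessions and the test case. Its aim is to "examine if there is decay, maintenance or further growth in the test case scenario". Its model is "Growth curve analyses will be used to test for linear change in observed suicide prevention skills across the three data collection points", where "time will be a count of days from baseline to subsequent observations". The results of interest are the overall slope and its predictors. The effect sizes rest on the same model: "Estimates of the means at each time point are derived from the model and used for effect size calculations". The section names no curvature term, change-point, session contrast or modality term.

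On modality, Design says of the practice sessions: "One practice interaction takes place in-person and the other uses a telehealth model. The order is randomized". For the last session, Standardized patient scenarios says: "The scenario used for the SP test case that all participants receive is an in-person female scenario". Modality is modelled under Exploratory analysis for hypothesis 3 ("Both time and modality will be entered as time varying covariates"), but the time factor there covers only the first and second interactions, so the test case is outside that model. The covariates listed under Data processing do not include modality.

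**The concern.** Decay, maintenance or further growth is a three-way question about what happens between session 2 and the test case. A single slope has no parameter for that interval: whatever sign it takes overall, it takes there too. The model-derived session means lie on the same line, so the effect sizes cannot reveal a turn either.

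Separately, randomising the order balances modality between sessions 1 and 2, but not between those two and the always in-person session 3. Any modality effect on the ratings therefore enters the slope. The analysis could report lasting improvement when skill had fallen back, or learning when there was none. Whether skills improve over the three encounters is a question announced in the Abstract and the Background, so the answer will be read.

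**Working it through.** The protocol gives no figure for this analysis, so there is none to reproduce.

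**Inputs from the protocol.** Telehealth share by session: .5, .5, 0 (Design; Standardized patient scenarios). Practice sessions fall within about four months, at least one month apart, with the test case at about six months (Procedures). 108 participants at 1:1 give about 54 in the experimental arm. The equivalence margin for modality is .20.

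**Assumed.** Session days, true session means, and the telehealth handicap h (.2, .3, .5 SD).

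**Formula.** With common session times, the mean linear-growth slope is b = Σ(t − t̄)y / Σ(t − t̄)².

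**Shape, days 0, 60, 150.** t̄ = 70; deviations −70, −10, +80; Σ(t − t̄)² = 4900 + 100 + 6400 = 11400. For true means 0, .40, .20:

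- b = (−10 × .40 + 80 × .20)/11400 = 12/11400 = .00105 per day.
- Fitted means: .126, .189, .284.
- Fitted change, session 2 to 3: 90 × 12/11400 = +.095 SD. True change: −.20 SD.

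**Shape, equal spacing (0, 75, 150).** The slope weights multiplied by the 150-day span are −1, 0, +1, so session 2 drops out of the slope:

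| Pattern | True means | Slope × span | Fitted session 3 − 2 | True session 3 − 2 |
|---|---|---|---|---|
| Growth | 0, .25, .50 | +.50 | +.25 | +.25 |
| Maintenance | 0, .50, .50 | +.50 | +.25 | 0 |
| Decay | 0, 1.00, .50 | +.50 | +.25 | −.50 |

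The three outcomes to be distinguished give the same result. At days 0/90/150 the decay pattern gives a steeper rise than steady growth (.59 against .49). At 0/30/150 it gives .18 against .45, still positive.

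**Modality, no true change.** Expected session means are −h/2, −h/2, 0. At days 0, 60, 150:

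- b = (70h/2 + 10h/2)/11400 = 40h/11400.
- Rise over 150 days = 6000h/11400 = .526h: .105, .158 and .263 SD for h = .2, .3 and .5.

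Over the schedules tried, the multiplier ran from .43 to .54. At equal spacing the artefact is h in learners who start with telehealth and zero in those who start face-to-face.

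**Simulation.** 54 learners, three sessions, gaps drawn from 30–120 and 30–90 days, total SD 1, within-person correlation .3, .5 or .7, 2000 runs per setting, within-person regression.

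- No learning, linear model: significant slope in 4–5% of runs at h = 0, 9–14% at h = .2, 13–23% at h = .3 and 24–49% at h = .5.
- True means 0, .6, .3 with h = 0: average slope +.34 to +.35 SD per 150 days, against +.31 for steady growth (0, .15, .3).
- Modality added to the linear model only: the no-learning slope returns to about zero (4–6% significant), but the decay pattern still shows about +.41 SD per 150 days.
- Session factor plus modality: the session 3 − 2 contrast averages −.30 for the decay pattern, and about 0 with 4–6% rejection when nothing changes. Both changes are needed.

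**The case against.** The strongest reply concerns modality. The article is condensed and does not say modality is excluded. Power analyses says covariates go into all models, and the neighbouring multilevel model already carries modality. No passage says telehealth scores lower: procedures are described as the same, scenarios as matched for difficulty, and equivalence is to be tested. A telehealth advantage would bias the slope downward instead. This makes the modality half conditional. It does not remove it, because the listed covariates omit modality and the model that includes it stops before the test case. A difference at the protocol's own .20 margin would still add about .10 SD.

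On shape, the failure is not universal: a fall taking session 3 well below session 1 would still give a negative slope. A linear model in actual days is also a conventional, parsimonious choice for about 54 learners with uneven spacing, and it does address the stated interest in overall slope and its predictors. Those points stand, but they do not make one slope answer the decay, maintenance or growth question set in the same section.

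Finally, the analysis is exploratory, confined to one arm and acknowledged to have limited power. That limits the consequence, not the mismatch.

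**Conclusion.** The concern holds. The shape problem follows from the stated model and the stated aim alone; only the illustrative size (+.095 fitted against −.20 true) depends on the assumed means and days. The modality problem requires a real modality difference, whose size and direction the protocol does not give. For a handicap of .20 to .50 SD the spurious rise is .11 to .26 SD over 150 days at days 0, 60, 150. It also takes the absence of a modality term from the published text, which a fuller plan could change. The primary ANCOVA at the test case is unaffected. The model should be changed before the three-session results are analysed.

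**What to change.** Replace the single slope with session as a three-level factor, or with a two-piece slope in days with its knot at session 2. Include a person random effect and modality as a time-varying covariate. Report two contrasts, each with a confidence interval: session 2 minus session 1 (learning) and test case minus session 2 (decay, maintenance or further growth). Base the effect sizes on these means.

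The two-piece version suits the protocol better where spacing varies, because it keeps days as the time scale and lets predictors of change act on each segment. The session factor gives up the days scale.

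Two caveats should be stated. The modality effect is identified from the randomised order in sessions 1 and 2, and is assumed to carry over to session 3. The test-case scenario always comes last, so a scenario difference cannot be separated from the final contrast, even though the scenarios are described as matched.

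The cost is one or two extra parameters and slightly wider intervals, with no new data. Precision stays modest: in the simulation a true fall of .30 SD was significant in about 38% to 72% of runs, depending on within-person correlation. The interval should therefore carry the conclusion, and a non-significant contrast should not be reported as maintenance.
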